### Outcome measures and process indicators

Primary endpoint is the number of patients that has an ECV performed. Secondary endpoints are guidelines' adherence rates, complications of ECV, the number of fetes that are in cephalic position at delivery, the number of caesarean sections and the perinatal condition of mother and child. Moreover, we will assess patients' knowledge (e.g. ECV, breech delivery, caesarean section), patients' decisional conflict and patients' satisfaction. We will also calculate costs of both implementation interventions and medical interventions. In case one or both implementation interventions are effective, their cost-effectiveness will be assessed.

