**Method/design:**

The ultimate purpose of this implementation study is to improve counselling of pregnant women and information of clinicians to realize a better implementation of ECV.

The first phase of the project is to detect the barriers and facilitators of ECV. The next step is to develop an implementation strategy to inform and counsel pregnant women with a breech presentation, and to inform and educate care providers. In the third phase, the effectiveness of the developed implementation strategy will be evaluated in a randomised trial. The study population is a random selection of midwives and gynaecologists from 60 to 100 hospitals and practices. Primary endpoints are number of counselled women. Secondary endpoints are process indicators, the amount of fetes in cephalic presentation at birth, complications due to ECV, the number of caesarean sections and perinatal condition of mother and child. Cost effectiveness of the implementation strategy will be measured.

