After the pilot study a cluster randomised controlled trial will be performed in which two implementation strategies will be evaluated: a patient centred strategy and a health care provider (midwife and gynaecologist) centred strategy. In the randomised clinical trial, we will allocate centres and their regions at random to four groups: A. Patient centred strategy alone, B. Healthcare providers-centred strategy alone, C. Both the patient and healthcare provider centred strategies, D. No specific implementation intervention.

Up to 30% of eligible patients are not offered an ECV attempt and up to 40% of counselled patients do not choose for ECV, which might be the result of insufficient information. With the decision aid we intend to increase the number of well informed patients from 50 to 80%. To correct for the degree of similarity among responses within a cluster, a intra-cluster correlation coefficient of 0.10 was integrated in the power analyses. To be able to show the difference of 30% with a power of 80% and an alpha error of 5%, we need 20 clusters of a 30 patients each. The gynaecologists in the participating hospitals will give informed consent for this trial to confirm that they will treat their patients conform one of the four strategies were they will be allocated to, as long as the trial is open for inclusion.

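### The primary endpoint is stated two ways, and the sample size and its 80% power belong to a third quantity that is primary in neither place

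*Protocol article*

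**What the plan says.** Three parts of the Protocol article bear on the primary endpoint.

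- Abstract, Method/design: "Primary endpoints are number of counselled women".
- Outcome measures and process indicators: "Primary endpoint is the number of patients that has an ECV performed". Guideline adherence, complications, presentation at delivery, caesarean sections and perinatal condition follow as secondary. After them comes: "Moreover, we will assess patients' knowledge (e.g. ECV, breech delivery, caesarean section), patients' decisional conflict and patients' satisfaction".
- Evaluation of the developed implementation strategies design, where the sample size is set: "With the decision aid we intend to increase the number of well informed patients from 50 to 80" per cent. The power statement follows: "a intra-cluster correlation coefficient of 0.10 was integrated in the power analyses", then "To be able to show the difference of 30% with a power of 80% and an alpha error of 5" per cent, "we need 20 clusters of a 30 patients each". On allocation: "we will allocate centres and their regions at random to four groups".

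The sample-size paragraph opens with two background rates: up to 30% of eligible women are not offered ECV, and up to 40% of those counselled do not choose it. It sets no target for either.

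**The concern.** Being counselled, being well informed and having an ECV are successive steps, and the article's own figures keep them apart. If at most 30% are not offered ECV, at least 70% are, so a starting value of 50% well informed cannot be the counselling rate. If up to 40% of counselled women decline, the counselling rate cannot stand in for the ECV rate either.

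Two things are at stake. With two quantities each called primary, a reader cannot tell which result decides whether a strategy worked. The outcome section also makes the cost-effectiveness assessment conditional on an effective strategy, so the choice decides whether that analysis is done. And the stated 80% power will be read as applying to the primary endpoint, whichever that is, when it was calculated for something else.

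**Working it through.** **1. Reproducing the plan's figure.** Inputs from the sample-size paragraph: 50% and 80% well informed, power 80%, alpha 5% (taken as two-sided, since sidedness is not stated), 30 patients per cluster, intra-cluster correlation 0.10, four groups (equal allocation assumed).

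- Individuals per arm = [z(0.975)·√(2·p̄·q̄) + z(0.80)·√(p1q1 + p2q2)]² / (p2 − p1)², with p̄ = 0.65: [1.960·√0.455 + 0.842·√0.41]² / 0.09 = 38.5, so 39.
- Design effect = 1 + (30 − 1)·0.10 = 3.9.
- 39 × 3.9 = 152.1 per arm = 5.07 clusters of 30. Over four arms: 20.3 clusters, about 608 patients, against 20 × 30 = 600 stated.

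The figure reproduces as a pairwise comparison of 5 versus 5 clusters. Its power is 80% with the pooled-variance normal formula, 83% unpooled, and 72% with a noncentral t on 8 degrees of freedom. All of these are for well informed, 50 to 80%.

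**2. Rates for the two stated primary endpoints.** The article states none, so these are assumptions.

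- *ECV performed.* If both background rates are at their maximum, the control rate is 0.70 × 0.60 = 42%. Because both are upper bounds, 42% is the lowest value that paragraph implies. The Background section puts the true rate probably below 50%, so I use 42% and 50%. Counselling every woman at unchanged 60% acceptance would give 1.00 × 0.60 = 60%.
- *Counselled.* Treating offered as counselled, the control rate is at least 70%. A 30-point gain from 70% would need 100%.

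**3. Power with the existing clusters.** With k clusters per arm, effective n = 30k/3.9, which is 38.5 for k = 5 and 76.9 for k = 10. SE = √[(p1q1 + p2q2)/effective n]. The normal unpooled power is Φ[(p2 − p1)/SE − 1.960].

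Example, ECV 42 to 60%, k = 5: SE = √[(0.2436 + 0.2400)/38.5] = 0.112; 0.18/0.112 = 1.605; power = Φ(−0.355) = 36%. The pooled formula gives 35%, and the t version 29%.

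Each range below runs from the t-based to the unpooled normal value.

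| Endpoint and assumed change | 5 v 5 clusters | 10 v 10 clusters |
|---|---|---|
| Well informed, 50 to 80% (plan's basis) | 72-83% | 97-98% |
| ECV performed, 42 to 60% | 29-36% | 57-62% |
| ECV performed, 50 to 70% | 36-45% | 69-73% |
| ECV performed, 50 to 80% | 72-83% | 97-98% |
| Counselled, 70 to 90% | 51-62% | 86-89% |

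The 10 v 10 column applies if the four groups are analysed as a 2 × 2 factorial on one margin. The article does not say this, but the groups allow it. The same intra-cluster correlation is assumed for every endpoint.

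**The case against.** The strongest reply is that the article describes a provisional trial. The section on evaluating the strategies says a detailed trial protocol will be written after the first phase, and a pilot and ethical approval come first. That makes a post hoc choice of endpoint less of a threat than it would be in a final protocol. It does not settle the contradiction: this text already fixes a primary endpoint twice and a sample size once, and the later protocol inherits the ambiguity unless someone resolves it.

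A second reply is that power may be adequate after all, and this stands in part. A reader might infer that the trial could not detect a realistic effect on its primary endpoint. The document does not support that. A rise in ECV from 50 to 80% has the same power as the plan's own scenario, and counselling from 70 to 90% has 86-89% on a factorial margin.

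A reader might also take 42% as the plan's own baseline. It is only the product of two upper bounds. The Background reports 4 to 33% not offered and self-reported ECV rates of 60 to 70%, which it thinks too high; the abstract puts implementation at no more than 50 to 60%.

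Nor can a gain in being informed be converted into a definite gain in ECV, since the article gives no uptake rates by information status. The Israeli surveys in the Background, where awareness rose and willingness fell, compare two calendar years and measure having heard of ECV. They do not show what a decision aid would do.

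**Conclusion.** The point holds. The primary endpoint is stated in two incompatible ways, and the 80% power belongs to a third quantity that is primary in neither statement. This follows from the text alone and needs no modelling. The sample-size arithmetic is sound for the quantity it uses.

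What cannot be concluded is that power is below 80% for the stated endpoints. The documents leave it undetermined: on the assumed rates it runs from about 29% (ECV 42 to 60%, pairwise) to 80% or more (ECV 50 to 80%, or counselling 70 to 90% on a factorial margin). Those figures assume a two-sided 5% test, equal allocation, an intra-cluster correlation of 0.10 for every endpoint and no multiplicity correction.

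**What to change.** Name the same single primary endpoint in the abstract and in the outcome section, defined as a proportion of eligible women with breech presentation rather than a number. List the other two quantities as secondary.

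In the sample-size paragraph, state the assumed control rate for that endpoint and either the power for a stated target or the difference that the existing 20 clusters can detect. Say whether this refers to pairwise arms or a factorial margin. If 50 to 80% well informed is to remain the power basis, make well informed the primary endpoint throughout; the present 20 clusters then match it.

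The cost is a wording change in three places and possibly a less favourable stated power. Stating this correctly needs no extra patients or data. If the authors choose ECV performed or counselling and want 80% power for a smaller effect than the design can detect, enlarging the trial is a separate decision, which they can then make knowingly.

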**Discussion:**

This study will provide evidence for the cost effectiveness of a structural implementation of external cephalic versions to reduce the number of breech presentations at term.

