The number of women with a breech presentation considering ECV and their knowledge about the procedure are unknown in the Netherlands. Until publication of the new NVOG and KNOV guidelines in 2001 and 2002, ECV used to be a controversial intervention. Since the introduction of these guidelines, there is no evidence for a raise in the number of ECVs performed. However, the number of birth in breech presentation at term is stable since 2002, indicating a low implementation grade of ECV.

Implementation requires a clear and deliverable evidence based message [13]. However, there are often major discrepancies between best evidence and practice, resulting in a large variation between professionals [14-17]. Based on this national and international literature, two main barriers for ECV implementation are identified 1) lack of patients' knowledge about risk for and consequences of ECV and breech delivery 2) the attitude and knowledge of midwives and gynaecologists towards ECV.

This study will show us if an implementation strategy, tailored on main barriers combining both patient and health care provider interventions, is more cost-effective than usual care. We will also evaluate the process of implementation to ascertain which elements of the strategy can be particularly associated with successful implementation of ECV. Moreover, our proposal is a collaborative effort of midwives and gynaecologists, and is supported by both the KNOV and NVOG.

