## Methods/Design

### Aims

The main objective of this study is to assess barriers and facilitators of implementation of ECV in the Netherlands. We would like to create a broad social basis and awareness for the need of cooperation in care for women with a fetes in breech position. An innovative implementation strategy will be developed based on improved patient counselling and thorough instructions of health care providers for counselling.

Research questions are: What are barriers and facilitators of implementation of ECV in the Netherlands? What are the costs and effects of an innovative implementation strategy based on improved patient counselling and information of health care providers to implement the guidelines on ECV for breech presentation? What is the feasibility of this implementation strategy?

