### Evaluation of the developed implementation strategies design

A cluster randomised controlled trial with an economic evaluation will be performed alongside. Ethical approval will be requested before the start of this part of the study. Information on counselling of patients, required for ethical approval, will be specified in the first phase of the trial. A set of quality indicators will be extracted from the NVOG and KNOV guidelines. The indicator development will be performed according to the RAND-modified Delphi method [21]. First of all, key recommendations from the guidelines will be extracted by two or three experts, the project leaders. Subsequently, the clinical relevance of all key recommendations for patient's health benefit and efficacy will be tested in two rounds among an independent panel of 12-15 experts (KNOV and NVOG guideline writers, KNOV and NVOG members, quality of care experts and patients). The key recommendations with the highest scores will be selected and made ready for use, in measurable elements (process indicators). Moreover, measurement instruments will be developed and the participating hospitals will be informed about the study. A detailed protocol on the randomised controlled trial will be written after finishing the first phase.

This is a requirement to receive further funding of the further project. This protocol is in development; it depends mainly in the outcome of the first phase. This will be followed by a pilot, feasibility study where two different implementation strategies will be tested in four participating hospitals, one primary care centre specialised in ECV and one independent midwifery practice. Before the pilot study starts, baseline characteristics and primary and secondary outcomes will be measured with questionnaires and data gathering on amount of version attempts, outcomes after ECV and caesarean section rate. The data gathering lists and questionnaires will also be developed during the first phase.

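### The cost-effectiveness assessment is made to depend on an undefined finding of effectiveness, which contradicts the unconditional economic evaluation stated elsewhere in the protocol

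*Protocol article*

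**What the plan says.** All references are to the protocol article.

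- **The condition** (Outcome measures and process indicators): "In case one or both implementation interventions are effective, their cost-effectiveness will be assessed". The sentence before it carries no condition: "We will also calculate costs of both implementation interventions and medical interventions".
- **Abstract, Method/design**: "Cost effectiveness of the implementation strategy will be measured".
- **Abstract, Discussion**: "This study will provide evidence for the cost effectiveness of a structural implementation of external cephalic versions".
- **Background**: the study is to show whether a strategy "combining both patient and health care provider interventions, is more cost-effective than usual care".
- **Methods overview**: evaluating cost-effectiveness is listed as a step of the project, again without a condition.
- **Evaluation of the developed implementation strategies design**: "A cluster randomised controlled trial with an economic evaluation will be performed alongside".
- **Aims**: a research question asks "What are the costs and effects of an innovative implementation strategy".

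The section on the trial design allocates centres to four groups: patient strategy, provider strategy, both, and neither. No section says which endpoint, contrast or threshold makes an intervention effective.

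**The concern.** Two things are wrong with the conditional sentence.

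First, it contradicts the rest of the document. Five other places present cost-effectiveness or an economic evaluation as something the study will deliver. One sentence makes it contingent on the result.

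Second, the rule is a poor one. Whether a strategy is good value depends on the cost difference and the effect difference taken together, with their uncertainty. A strategy that misses an effectiveness criterion has not been shown to have no effect, and it has not been shown to be poor value. With four groups, a decision maker also wants the three active options compared with each other, not only those that passed a test against no intervention.

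The stake is that a central aim may go unanswered. In addition, if cost-effectiveness is published only after favourable effect results, the published figures will on average rest on effect estimates that are too large. Because the criterion is open, whether it has been met could also be decided after the results are seen.

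**Working it through.** **1. The plan's own figure.** Inputs from the trial design section: 50% versus 80% well-informed patients, power 80%, alpha 5% (taken as two-sided), intra-cluster correlation 0.10, 30 patients per cluster.

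- Two proportions, pooled variance, no continuity correction: 39 per group.
- Design effect: 1 + (30 − 1) × 0.10 = 3.9.
- Per group: 39 × 3.9 = 152.1, or 152.1 / 30 = 5.07 clusters.
- Four groups: 4 × 152.1 = 608, or 20.3 clusters. The stated 20 × 30 = 600 agrees to about 1%.

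The stated size thus fits about 5 clusters in each of four groups (an equal split is assumed). A factorial analysis then tests each strategy on 10 versus 10 clusters.

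**2. Assumptions for the consequence.** Effective is read as two-sided p<0.05 in favour of the strategy; the 5% alpha is the only threshold in the document. The assessment is triggered if either strategy qualifies, so the relevant event for no analysis is that neither does.

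**3. Effect sizes.** The first is the planned 50% versus 80%. The second is a smaller effect on ECV performed, the endpoint named in the outcome section. The trial design section says up to 30% of eligible women are not offered ECV and up to 40% of those counselled decline, which gives 0.70 × 0.60 = 42%. The comparison value of 55.8% (a 13.8-point rise) is purely illustrative and does not come from the document.

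**4. Simulation.** Beta-binomial clusters of 30, correlation 0.10, t-test on cluster proportions, 100,000 trials, 10 versus 10 clusters:

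| True rates | Power per strategy | Mean significant estimate / truth |
|---|---|---|
| 50% v 80% | 0.96 | 1.02 |
| 42% v 55.8% | 0.37 | 1.56 |

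- Chance that neither strategy qualifies, treating the two tests as independent: (1 − 0.37)² ≈ 0.40 at the smaller effect, and (1 − 0.96)² ≈ 0.002 at the planned one.
- Simulating all four groups with two additive 13.8-point effects gives 0.40 for neither and an exaggeration of 1.54.
- Two additive 30-point effects from 50% would exceed 100%, so the planned-effect figure describes the margins only. If just one strategy works at the planned size, it is missed about 4% of the time.

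**5. Cross-check by normal approximation** (50% control rate, 10 versus 10 clusters, exaggeration averaged over z > 1.96):

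| True difference | One strategy missed | Both missed (independent, equal effects) | Exaggeration |
|---|---|---|---|
| 30 points | 2% | <0.1% | 1.01 |
| 20 points | 27% | 7% | 1.17 |
| 15 points | 52% | 27% | 1.44 |
| 10 points | 76% | 58% | 2.03 |

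The pattern is the same: nothing to speak of at the planned effect, and a material loss below about 20 points.

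**The case against.** The best defence is that this is one sentence in an article which says a detailed trial protocol will follow, and that the damage is small. Several parts of that stand.

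- **Significance is not stated.** A reader might infer that the evaluation is conditional on a significant result. The document says effective and names no test, so every figure above depends on an assumption.
- **The research question in Aims is not lost.** It asks for costs and effects. Costs are calculated unconditionally and the effect evaluation under Implementation study is unconditional, so both can be reported separately. Only the step that combines them is conditional.
- **Single pairwise contrasts overstate the risk.** With 5 versus 5 clusters the simulated miss rate is 29% (50% v 80%) to 81% (42% v 55.8%), with exaggeration of 1.15 and 2.0 times. The trigger is either strategy, and a factorial analysis uses 10 versus 10 clusters, so these are not the chances of having no analysis.
- **Cost per extra ECV is not shown to be understated by about half.** That would divide a fixed cost difference by an inflated effect. The plan counts medical costs, and the Background puts a caesarean at 1,500 Euros more than a vaginal delivery, so the cost difference moves with the effect.
- **A result that is always too favourable is not supported.** The bias is an average, and it is about 1.02 times at the planned effect.
- **The comparator is no specific intervention.** Each strategy adds cost, so the case of a cheaper strategy with similar effect has limited reach against that group. It keeps its force between the active groups.

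The provisional status does not rescue the sentence. The article does not leave the matter open; it states a rule, and the rule conflicts with its own aims.

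**Conclusion.** The point holds as an internal contradiction and a badly chosen rule. The condition conflicts with the unconditional economic evaluation in the Abstract (Method/design and Discussion), the Background, the Methods overview and the trial design section. The conflict needs no assumption.

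The practical size does need assumptions: effective meaning two-sided p<0.05, an equal split, a factorial analysis and the plan's correlation of 0.10. Under these, the chance of no cost-effectiveness analysis is negligible at the planned 30 points and about 40% for a rise in ECV from 42% to 56%. Average exaggeration given significance runs from about 1.02 to 1.55 times. The smaller effect is illustrative, but it is not far-fetched: the 30-point target concerns well-informed patients, whereas the primary endpoint in the outcome section is ECV performed. This should be corrected before the detailed trial protocol is written; it does not threaten the trial itself.

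**What to change.** Delete the condition. State that the cost-effectiveness analysis will be carried out for all four randomised groups whatever the effect result. Take the cost and effect differences from a model that respects clustering, and report their joint uncertainty, for example as net benefit or a cost-effectiveness acceptability curve.

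This guarantees that the stated aim is answered and removes the selection of which results get reported. It does not alter the estimate in a trial that would have been positive anyway. The sample size stays at 20 clusters of 30 and no further data are needed, since costs and effects are collected in any case. The price is a little more analysis.
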